### Data analyses

Generalized Linear Mixed Models will be used to test intervention effects for binary outcomes and linear mixed models for continuous outcomes [43, 44]. These models account for both fixed and random effects and are particularly useful in analysing longitudinal and nested data (e.g., time within students, students within school classes). To test the efficacy of the intervention, we will test the variables “study group”, “time” and their interaction “study group x time” as predictors of the outcome criteria assessed at follow-up. If necessary, we will control for baseline differences by adding additional baseline variables as covariates to the models. We will conduct both (1) intention to treat analyses and (2) complete case analyses considering all study participants with available follow-up data. For ITT analyses, we will use multiple imputation procedures as described elsewhere [45].

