### Randomisation and allocation concealment

To avoid spill-over effects within school classes, we will conduct a cluster-randomised controlled trial using school class as a randomisation unit. Due to the heterogeneity of students in the different secondary schools, we will use a separate randomisation list for each school (stratified randomisation). Furthermore, to approximate equality of sample sizes in the study groups, we will use block randomisation with computer generated randomly permuted blocks of 4 cases [29].

Junior scientists supervising the baseline assessment will be blinded to the group allocation of school classes. In addition, group allocation will not be revealed to participants until they had provided their informed consent, username, mobile phone number, and baseline data. Furthermore, the research assistants who perform the computer-assisted follow up assessments for primary and secondary outcomes will be blinded to the group allocation.

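### Randomisation is stratified by school, but the described analysis has no school term; if school is left out of the models, the follow-up comparison is conservative by an amount the document does not fix

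*Protocol article*

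**What the plan says.** Protocol article, Randomisation and allocation concealment: the trial is a "cluster-randomised controlled trial using school class as a randomisation unit". The section then makes school a design factor and gives the reason: "Due to the heterogeneity of students in the different secondary schools", "we will use a separate randomisation list for each school (stratified randomisation"). Within each list it uses "block randomisation with computer generated randomly permuted blocks of 4 cases".

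Protocol article, Data analyses: generalised linear and linear mixed models are planned and described as useful for nested data. The levels are given as examples, introduced by e.g.: "time within students, students within school classes". The tested terms are stated without any such qualifier: "we will test the variables “study group”, “time” and their interaction “study group x time” as predictors of the outcome criteria assessed at follow-up". The covariate rule is conditional: "If necessary, we will control for baseline differences by adding additional baseline variables as covariates to the models".

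School is not named as a random effect, a fixed effect or a covariate. No sentence says that it will be left out.

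**The concern.** A stratification factor belongs in the model because of the design, not because of what the baseline table shows. The authors consider schools different enough to justify separate lists, yet the analysis they describe stops one level lower. The conditional covariate rule does not close the gap: stratifying makes the arms less likely to look unbalanced on school, so a rule triggered by baseline differences is unlikely to bring school in.

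When arms are balanced within schools, between-school variance largely drops out of the true variance of the group contrast. A model with class as its top level cannot see this. It puts school variance into the class effect and counts it in the standard error. At stake is avoidable imprecision: wider intervals and a test below its nominal 5% level. Validity and the planned power are not at stake.

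**Working it through.** **Inputs from the Sample size calculation section.** Odds ratio 0.60; control prevalence 25% (problem drinking) and 22% (smoking); two-sided 5%; 80% power; 370 and 410 per group before clustering; 13 participants per class; ICC 0.05; about 100 classes. Neither the number of schools nor any between-school variance is given.

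**Reproducing the plan.** An odds ratio of 0.60 turns 25% into 16.67% and 22% into 14.47%. The two-proportion formula without continuity correction gives 372 and 413 per group (stated 370 and 410), so the plan is reproduced to rounding. The design effect is 1 + 12 × 0.05 = 1.60; 410 × 1.60 = 656 per group, 1312 in total; 1312 / 13 ≈ 101 classes. The plan takes no credit for stratification.

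**Effect of leaving school out, full balance within schools.** I take 0.05 as the total correlation between classmates and assume that a share s of it lies between schools.

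- The design effect can be written 13 × 0.05 + 0.95 = 1.60. Without the school part it is DE = 1.60 − 13 × 0.05 × s = 1.60 − 0.65s.
- Modelled over true standard error = √(1.60 / DE).
- Actual test size without school = 2[1 − Φ(1.96 × √(1.60 / DE))].
- Power for smoking at 656 per group, with D = 0.22 − 0.1447 = 0.0753, null standard error se0 = √(2 × 0.1824 × 0.8176 / 656) = 0.0213 and se1 = √((0.22 × 0.78 + 0.1447 × 0.8553) / 656) = 0.0212. With school: Φ[(D − 1.96 se0 √DE) / (se1 √DE)]. Without school: the same, with √1.60 in place of √DE in the numerator.

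| s (assumed) | DE | SE ratio | Test size without school | Power with school | Power without |
|---|---|---|---|---|---|
| 0 | 1.600 | 1.00 | 5.0% | 79.8% | 79.8% |
| 0.10 | 1.535 | 1.02 | 4.5% | 81.4% | 80.3% |
| 0.25 | 1.438 | 1.055 | 3.9% | 83.9% | 81.1% |
| 0.50 | 1.275 | 1.12 | 2.8% | 87.9% | 82.5% |

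**Incomplete blocks.** In a block of 4 with two classes per arm, two given classes share an arm with probability 1/3 and differ with probability 2/3, so the expected product of their arm signs is −1/3. With k classes per school (k ≤ 4), the fraction (k − 1)/3 of the school component is removed, and DE = 1.60 − 0.65s(k − 1)/3. For s = 0.25 and 0.50:

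- k = 2: DE 1.546 and 1.492, SE ratio 1.017 and 1.036.
- k = 3: DE 1.492 and 1.383, SE ratio 1.036 and 1.076.
- k = 4: the full-balance rows above.

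A simulation of class means on a linear scale (about 100 classes, 3000 runs) gave ratios of 1.01 to 1.02 for k = 2, 1.04 to 1.06 for k = 3, 1.04 to 1.13 for k = 4, and 1.04 to 1.11 for k = 6 to 8. Its own error is about 1/√6000 = 1.3%, so it agrees with the formula. I therefore put the inflation at about 1 to 4% for two classes per school.

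**Fixed or random school effect.** With two classes per school, school as a fixed effect raised the true standard error in the simulation from 0.0694 to 0.0822 (s = 0.25) and from 0.0685 to 0.0772 (s = 0.50).

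**Change-from-baseline contrast.** If baseline is one of the time points and school effects are constant over time, they cancel. Simulated ratios were 0.93 to 1.03, scattered around 1 with no systematic inflation.

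**The case against.** The nesting is introduced by e.g., so it illustrates why mixed models suit these data and is not a list of random effects. A reader might infer that the models will have time, student and class as their only levels. The document does not say so, and a fuller analysis plan may name school. This stands, and it is why the point is conditional. The tested terms and the covariate rule, however, carry no such qualifier, and school is in neither.

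A reader might also infer that the benefit of stratifying is thrown away. That goes too far. Balance within schools still lowers the true sampling variance whatever model is fitted; what can be lost is its recognition in the standard error.

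The interaction of group and time may be the test that matters, and for change from baseline the problem nearly disappears. This stands if baseline is modelled as an outcome time point. The section, however, speaks of outcomes assessed at follow-up, and the primary outcomes are set at month 18. On that reading the group contrast lies between classes and school variance does not cancel.

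Finally, the figures in the table are a best case, since they need full balance and an assumed share. This also stands. It limits the size, not the direction.

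**Conclusion.** The point holds as a conditional one. School is a stratification factor by design and is absent from the analysis as described. If it is left out, inference on a follow-up group contrast errs on the conservative side: no bias, no type I error inflation, and power still about 80% or a little more, because the sample size never counted on a stratification gain.

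The document does not allow one size to be stated. The 0 to 12% range for the standard error rests on an assumed school share of 0 to 50% of the ICC and on full balance of arms within schools. It is much smaller where schools contribute only two classes, and close to nil for a change-from-baseline contrast with constant school effects. The simulation is on a linear scale and only approximates the logistic mixed model. This is a worthwhile gain in precision, not a threat to the trial's validity.

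**What to change.** State in the Data analyses section that school, as the stratification factor, enters all primary and secondary models as a random intercept above class, irrespective of baseline differences. A random effect is preferable to a fixed one because schools with few classes, or with classes in one arm only, then still contribute to the group comparison.

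The cost is one model term; the separate randomisation lists already identify the school. If schools contribute few classes, the school variance may be estimated at or near zero, and the plan should say in advance how that will be handled. Settling this before outcome data are seen also removes a discretionary modelling choice.

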## Discussion

Substance use in adolescents and later adulthood and its related consequences represent a serious public health problem [27]. Although life-skills trainings were effective in preventing the onset and escalation of both problematic alcohol and tobacco use [7, 11, 30], the implementation and dissemination of the existing programs in schools represent serious challenges as they require large resources in terms of money and time [15]. In contrast to comprehensive school-based curricula, training and counselling via mobile phone is more economic and matches with the lifestyle and communication habits of the target group. Most adolescents are familiar with how to use mobile phones and typically use them on a daily basis for texting, taking photos, playing games etc. This is the first study testing the efficacy of a mobile phone-delivered life-skills training for substance use prevention among adolescents within a controlled trial.

Given that this program proves to be effective, it could be disseminated to various groups of adolescents, e.g. in schools or leisure time settings. A translation of the intervention content into other languages would easily enable program dissemination to adolescents in other regions and countries.

## Abbreviation

AUDIT-C: Short form of the alcohol use disorders identification test
